## A.8. Data analysis

### A.8.1. Summarize the statistical analysis strategy for each specific aim.

#### Analytical Plan.

Statistical analysis. Data analyses will be performed using SAS statistical software (Version 9.4 or higher, Cary, NC). Baseline descriptive characteristics will be summarized globally, and by intervention group, using frequencies and percentages for categorical variables, and means and standard deviations (median [Q1, Q3] for non-symmetric data) for inherently quantitative variables. Prior to conducting data analyses, we will audit the data for completeness and quality, including missing data. We will evaluate distributions to ensure that they meet assumptions of planned analyses (see below), including the detection of outliers.

Baseline equivalence. As outlined in the consort statement extension for cluster RCTs, random assignment by individual ensures that any differences in group characteristics at baseline are the result of chance rather than some systematic bias; however, in cluster RCT the risk of chance imbalance is greater as clusters rather than individuals are randomized. Therefore, to assess the degree to which randomization resulted in equivalent groups, we will assess if baseline variables are distributed differently between intervention groups. Baseline equivalence of student characteristics will be examined in two- and three-level hierarchical linear models, as appropriate, with an indicator for treatment arm. Baseline characteristics that demonstrate group nonequivalence will be controlled for in the analytic models.

Analysis of primary and secondary outcomes. Our primary analyses for Aim 1 will involve testing change in minutes of non-sedentary activity and HEI scores between standard Go NAPSACC and Go NAPSACC Enhanced groups at 6 (primary outcome) and 12 months (secondary outcome). Using maximum likelihood methods, we will use multi-level linear mixed models (PROC MIXED) with repeated measures to estimate change at 6 and 12 months and to test for statistical differences across groups in changes over time. Models will include random effect for cluster to account for covariance between participants within the same center as well as fixed effects for time, trial arm, time\*arm interaction. A proper error covariance structure will be chosen based on model fit indicated by model likelihood, Akaike Information Criterion and Bayesian Information Criterion. Residuals will be examined to check the assumptions of models. The results from the mixed models will be summarized with adjusted means and 95% confidence intervals (CI) by trial arm at each time point. To further explore the effect of the intervention, these analyses will be followed by sensitivity analyses that adjust for baseline variables distributed differently between intervention groups and examine completers only. Similar analyses will be completed for each secondary outcome: 1) provider weight, 2) provider device measured MVPA (Actigraph), 3) provider HEI score (ASA24), and 4) overall EPAO nutrition and PA environment scores. We will also use multi-level linear mixed models to examine secondary outcomes as longitudinal covariates and assess their association with longitudinal measures of primary outcomes, controlling for treatment, at 6 and 12 months.

Missing data and statistical models. All analyses will be conducted using the intention-to-treat principle (ITT), in which all available data on all randomized participants are included. This approach minimizes bias if individuals drop out of the trial for different reasons. Every effort will be made to obtain follow-up data on all patients randomized, whether or not they follow their assigned treatment. Our maximum likelihood approach assumes that any missing outcome data is missing at random (i.e., missing data including that due to drop-out can be dependent on any previously observed outcomes or treatment assignment). With this approach, we use all data that have been collected without regard to whether data are missing for a patient at another visit, including drop-out, and without explicit imputation of missing data. If the combined rate of missingness on variables is above 5%, we will consider imputing missing endpoint data using multiple imputation techniques and will assess the sensitivity of our results to various assumptions of missing data patterns.

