**A.8.3. Provide a compelling justification for the proposed sample size in terms of the likelihood of achieving each aim.**

Power analysis. This trial is powered to detect between group difference (Standard Go NAPSACC vs. Go NAPSACC Enhanced) of 5 units in HEI score and 1 minute per hour in non-sedentary PA. The sample size and power calculations for the proposed cluster RCT design depends on the following parameters: the number of child care centers, the number of students per school (~8; ~4 children x 2 classrooms), effect size (d), provider-level and center-level intra-class correlations (ICCs; ?), and the proportion of explained variance in school means by center-level covariates (R^2). We anticipate that on average about 8 children and 2 providers will participate at each child care center, and conservatively calculated sample size estimating 0% of variance can be accounted for by covariates. The ICCs observed in our previous work assessing preschool children's dietary intake and PA (R01 HL120969) were 0.04 and 0.07 for HEI score and 0.07 and 0.10 for non-sedentary PA at the provider- and center-levels, respectively. Based on previous studies at child care, the standard deviation of change in HEI score is estimated at 11 units and non-sedentary PA is estimated at 3 minutes per hour. Furthermore, we calculated power for each of the two primary comparisons using a type I error rate of 2.5%, thus keeping overall Type I error rate at 0.05. Sample size was initially calculated using assumptions associated with non-sedentary PA knowing that the higher ICC would require a larger sample size. This sample size was then used to conduct a power analysis for HEI score.

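### The primary model names one center random effect and no term that lets change vary by center; fitted as a center intercept, it would test the 6-month difference in change as if children were independent

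*Protocol*

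**What the plan says.** Protocol A.8.1 (Analysis of primary and secondary outcomes) describes the Aim 1 analysis as "testing change in minutes of non-sedentary activity and HEI scores" between arms, with 6 months primary and 12 months secondary. The method is a multi-level linear mixed model with repeated measures in PROC MIXED, used to "test for statistical differences across groups in changes over time". On clustering it says: "Models will include random effect for cluster to account for covariance between participants within the same center as well as fixed effects for time"; arm and the time-by-arm interaction complete the fixed effects. On the repeated measures it says: "A proper error covariance structure will be chosen based on model fit indicated by model likelihood", together with AIC and BIC. It names neither the subject level of that structure, nor a classroom effect, nor a center-by-time effect.

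A.8.3 takes a different view of the same contrast. For the spread it says "the standard deviation of change in HEI score is estimated at 11 units", and the same sentence gives 3 minutes per hour for non-sedentary PA. For clustering, the ICCs from the team's previous work "were 0.04 and 0.07 for HEI score and 0.07 and 0.10 for non-sedentary PA at the provider- and center-levels, respectively". The sizing therefore attaches both levels of clustering to the variance of change. A three-level structure does appear in A.8.1, but only for baseline equivalence, where characteristics "will be examined in two- and three-level hierarchical linear models".

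**The concern.** The treatment effect is a difference in change. A center effect that is constant over time enters a child's baseline and 6-month values equally and drops out of the difference. An error covariance that works within the child, whatever its form, cannot put covariance between children of one center back into that difference. Followed literally, the model gives change no between-center variance, although the sizing assumes that it has some.

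The design makes clustered change plausible. Under A.4.2, directors choose center goals and build their own action plans in both arms, and each Enhanced provider chooses a personal goal. Outcomes are collected largely during a two-day visit to each center, with child diet observed there, so children of one center may share the features of that visit.

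At stake are the p-values and confidence intervals for both primary outcomes, and the overall error rate of 0.05 that A.8.3 sets out to keep by testing each at 0.025.

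**Working it through.** **Inputs.** From A.8.3: 84 centers, 2 classrooms each, 4 children per classroom (672 children); differences of 1 min/hour (PA) and 5 units (HEI); SDs of change 3 and 11; ICCs provider/center 0.07/0.10 (PA) and 0.04/0.07 (HEI); 0.025 per outcome. Allocation is 1:1 by center (General Information). *Assumptions:* the PA SD, like the HEI SD, is an SD of change; tests are two-sided (sidedness is not stated); the ICCs apply to change (relaxed in step 5).

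**1. Reproduce the plan's power.** Variance of a center mean of change = SD² × [ICC_c + ICC_p/2 + (1 − ICC_c − ICC_p)/8]; SE of the arm difference = √(4 × variance / 84).
- PA: 9 × (0.10 + 0.035 + 0.10375) = 2.149; SE = 0.320; 1/0.320 = 3.126. Power is Φ(3.126 − 1.960) = 87.8%, or Φ(3.126 − 2.241) = 81.2% with the two-sided 0.025 critical value.
- HEI: 121 × (0.07 + 0.02 + 0.11125) = 24.35; SE = 1.077; 5/1.077 = 4.64; power above 99% either way.

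The stated 88% is matched with both ICCs applied to the SD of change, at the 1.960 critical value. With 68 centers the same formula gives 80.3% and 98.7%, against 81% and 98% stated. The sizing is thus consistent with clustered change.

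**2. What a center intercept does.** With value = fixed part + c(center) + e(child, time), change from baseline to 6 months = difference in fixed parts + e(6) − e(0). The term c is gone. The model SE of the contrast is √(4 × SD² / 672) = 0.231 (PA) and 0.849 (HEI).

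**3. SE ratio.** Design effect DE = 1 + 3(ICC_c + ICC_p) + 4 ICC_c.
- PA: 1 + 0.51 + 0.40 = 1.91; √1.91 = 1.38
- HEI: 1 + 0.33 + 0.28 = 1.61; √1.61 = 1.27

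**4. Type I error at two-sided 0.025.** 2 × [1 − Φ(2.241/√DE)].
- PA: 2 × [1 − Φ(1.622)] = 0.105
- HEI: 2 × [1 − Φ(1.766)] = 0.077
- With 3.2 children per classroom (20% child attrition, completers), DE = 1 + 2.2(ICC_c + ICC_p) + 3.2 ICC_c = 1.694 and 1.466, giving 0.085 and 0.064.

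Simulated null trials (84 centers, 8 children, 3 visits) agree. A center intercept with compound-symmetric within-child covariance rejected at 0.105 (PA) and 0.080 (HEI); with unstructured covariance, 0.116 and 0.074. With no clustering of change the compound-symmetric model rejected at 0.027.

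**5. If change is less clustered.** Half the sizing ICCs: 0.063 (PA) and 0.050 (HEI). A quarter: 0.043 and 0.037. If the quoted ICCs are instead ICCs of level, the result depends on how far center and classroom effects persist over time. Ranges cover both outcomes and an assumed within-child residual correlation of 0.2 to 0.7:

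| Correlation of center and classroom effects over time | Type I error at 0.025 |
|---|---|
| 1.0 | 0.025 |
| 0.9 | 0.031–0.053 |
| 0.8 | 0.038–0.080 |
| 0.5 | 0.058–0.145 |

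**6. When change may vary by center.** A t-test on center-mean change (82 df) rejected at 0.0245 (PA) and 0.026 (HEI) in simulation.

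**The case against.** The strongest reply is that the defect is read into silence. The protocol does not say that the cluster effect is an intercept only, and it leaves the error structure open. A.8.1 asks only for a summary of strategy, and a center-by-time term in a statistical analysis plan, which is not at hand, would be compatible with the wording. The stated purpose of the term, to capture covariance within a center, would be defeated by a model that loses it from the primary contrast. This stands in part: the inflation is conditional on the ordinary reading. It does not remove the point, because the sentence gives the term's purpose, lists the fixed effects, and names nothing that lets change differ between centers, while the sizing assumes that it does.

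A reader might infer that type I error simply is three to four times nominal. The documents do not support that. The ICCs are described as observed for dietary intake and PA, not for change, so inflation can run from none to more than fourfold.

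A reader might also count the missing classroom level as a second source of inflation. With balanced classrooms it is not: the center-mean test in step 6 has no classroom term and holds its level.

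Finally, A.8.1 speaks of minutes and A.8.3 of minutes per hour. That is a minor wording mismatch with no bearing on the standard errors.

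**Conclusion.** The point holds in conditional form. The stated model names no term for between-center variation in change, and so does not match the sizing. Fitted as a center intercept with within-child covariance, it understates the SE by a factor of about 1.38 (PA) and 1.27 (HEI), with type I error at two-sided 0.025 of about 0.105 and 0.077 on complete data. These figures rest on three assumptions: the intercept reading, the sizing ICCs taken as ICCs of change, and two-sided testing. Weaker clustering of change shrinks the excess; only its absence removes it. Because this concerns the primary test of both primary outcomes, the model should be settled in the text and not left to interpretation.

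**What to change.** In A.8.1, replace the single cluster effect with:
- a center-level random effect that varies over time (center-by-time, or an unstructured or compound-symmetric center covariance over the three visits);
- a within-child repeated-measures covariance;
- classroom-by-time for child outcomes, to match the sizing;
- REML with center-based degrees of freedom, for example Kenward-Roger, for the 6-month contrast.

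For provider outcomes use center-by-time only. With 168 providers in 84 centers of two classrooms there is about one provider per classroom, so a classroom-by-time effect could not be separated from the provider's own residual. A baseline-adjusted model of the 6-month value is not an equivalent substitute: it is a different estimator and, fitted to observed 6-month values, drops children without follow-up, whereas the protocol's missing-data paragraph commits to using all available data.

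The cost is a few lines of code and text, wider intervals and a somewhat harder fit. From the protocol's inputs, a clustered analysis of change has about 80–81% power for PA and 99% for HEI at two-sided 0.025. The modification form reports 43 subjects enrolled and enrollment open, so the wording could still be changed during enrollment.

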### A.8.2. If this is a pilot study, please describe the future study and say how its study design, aims, sample size, and methods differ from the pilot study you are proposing.

This is not a pilot study.

**A.8.3. Provide a compelling justification for the proposed sample size in terms of the likelihood of achieving each aim.**

Power analysis. This trial is powered to detect between group difference (Standard Go NAPSACC vs. Go NAPSACC Enhanced) of 5 units in HEI score and 1 minute per hour in non-sedentary PA. The sample size and power calculations for the proposed cluster RCT design depends on the following parameters: the number of child care centers, the number of students per school (~8; ~4 children x 2 classrooms), effect size (d), provider-level and center-level intra-class correlations (ICCs; ?), and the proportion of explained variance in school means by center-level covariates (R^2). We anticipate that on average about 8 children and 2 providers will participate at each child care center, and conservatively calculated sample size estimating 0% of variance can be accounted for by covariates. The ICCs observed in our previous work assessing preschool children's dietary intake and PA (R01 HL120969) were 0.04 and 0.07 for HEI score and 0.07 and 0.10 for non-sedentary PA at the provider- and center-levels, respectively. Based on previous studies at child care, the standard deviation of change in HEI score is estimated at 11 units and non-sedentary PA is estimated at 3 minutes per hour. Furthermore, we calculated power for each of the two primary comparisons using a type I error rate of 2.5%, thus keeping overall Type I error rate at 0.05. Sample size was initially calculated using assumptions associated with non-sedentary PA knowing that the higher ICC would require a larger sample size. This sample size was then used to conduct a power analysis for HEI score.

Using this information and Optimal Design 3.01, a sample size of 84 centers, with two 2-5-year-old classroom per center, and an average of 4 children per classroom, for a total of 672 children would allow us to detect a clinically meaningful difference in non-sedentary PA with 88% power at  $\alpha=0.025$  level of significance. This sample size also provides more than 99% power to detect a difference of 5 units in HEI score between the two study arms. Even with up to 20% attrition for centers and children, a completer's only analysis will still provide 81% and 98% power for change in non-sedentary PA and HEI score, respectively, which is higher attrition than we expect based on our previous trials. Based upon our sample size for our primary aims, we have included effect sizes that we will be powered to detect for our secondary outcomes with 80% power.

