**A.1.2. State the research question(s) (i.e., specific study aims and/or hypotheses).**

Our **central hypothesis** is that meeting the interests and demands of providers, via a Go NAPSACC weight management program, will improve the health behaviors of the provider, subsequently boost instruction and modeling of these healthy lifestyle behaviors, and enhance Go NAPSACC's effect on the child care's use of healthy weight practices for the children in its care. Centers will be randomly assigned to 1) standard "Go NAPSACC" or 2) "Go NAPSACC Enhanced" (with a provider weight management component). Assessments will be completed at baseline, 6, and 12 months to address the following aims:

Aim 1. Improve dietary quality and PA behaviors of 2-5-year-old children.

H1a: Children enrolled at Go NAPSACC Enhanced centers will demonstrate greater improvements in diet quality and PA at 6 months relative to those in the standard Go NAPSACC arm (primary hypothesis).

H1b: Children enrolled at Go NAPSACC Enhanced centers will maintain greater improvements in diet quality and PA at 12 months relative to the standard Go NAPSACC arm.

Aim 2. Improve weight and weight related behaviors (dietary intake and PA) of child care providers.

H2: Providers enrolled at Go NAPSACC Enhanced centers will manifest greater improvements in weight, diet quality, and PA at 6 and 12 months relative to standard Go NAPSACC arm.

Aim 3. Improve the nutrition and PA environments at child care centers.

H3: Centers receiving Go NAPSACC Enhanced will make greater improvements in provisions, practices, and policies around children's healthy eating and PA at 6 and 12 months relative to standard Go NAPSACC.

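### On the protocol's own inputs, two-sided testing at 0.025 gives about 80% power for non-sedentary PA, not 88%, and no two-sided reading of the 20% attrition gives 81%

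*Protocol*

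**What the plan says.** A.8.3 powers the trial for a difference "of 5 units in HEI score and 1 minute per hour in non-sedentary PA". Each of the two primary comparisons was powered "using a type I error rate of 2.5%, thus keeping overall Type I error rate at 0.05". The SD of change is 3 min/h for PA and 11 units for HEI. The ICCs are "0.07 and 0.10 for non-sedentary PA at the provider- and center-levels, respectively"; for HEI they are 0.04 and 0.07. Covariates are assumed to explain none of the variance. PA set the sample size because its ICCs are higher.

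The section concludes that 84 centers, with two classrooms each and four children per classroom (672 children), "would allow us to detect a clinically meaningful difference in non-sedentary PA with 88% power" at alpha 0.025, with more than 99% for HEI. If as much as a fifth of both groups is lost, the section claims for those who complete: "only analysis will still provide 81% and 98% power for change in non-sedentary PA and HEI score, respectively".

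Sidedness is not stated. The Analytical Plan in A.8.1 intends "to test for statistical differences across groups in changes over time", while H1a in A.1.2 is directional: children in Enhanced centers "will demonstrate greater improvements in diet quality and PA at 6 months relative to those in the standard Go NAPSACC arm".

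**The concern.** A.8.3 supplies nearly every input, so the figures can be checked, and the PA figures do not come out at a two-sided 0.025. PA has the least margin of the two primary outcomes. On the two-sided reading, with 20% lost at both levels, the chance of missing a true 1 min/h effect is about 35%, against the 19% implied by the stated 81%.

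The retention discussion in A.7.1 and the attrition paragraph in A.7.4 both judge losses by their effect on power, so they need correct reference figures. The Post Approval Submissions section shows enrollment still open with 43 subjects enrolled, so a correction is timely.

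**Working it through.** **Inputs (A.8.3).** PA: difference 1, SD 3, provider ICC ρp = 0.07, center ICC ρc = 0.10. HEI: difference 5, SD 11, ρp = 0.04, ρc = 0.07. R² = 0; J = 84 centers, 1:1; 2 classrooms; n = 4 children per classroom; alpha 0.025.

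**Formula (three levels).**
Var(center mean) = SD² × [ρc + ρp/2 + (1 − ρc − ρp)/(2n)]
SE of the difference = √(4 × Var / J); noncentrality = difference / SE.
Power is given from the noncentral t with J − 2 df, then from the normal approximation.

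**PA, full data.** Var = 9 × (0.10 + 0.035 + 0.83/8) = 9 × 0.23875 = 2.149. SE = √(4 × 2.149/84) = 0.320. Noncentrality = 1/0.320 = 3.126. Cross-check: the design effect is 8 × 0.23875 = 1.91; 336/1.91 = 175.9 effective children per arm; 3 × √(2/175.9) = 0.320.

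- *Reproducing the stated 88%:* a normal critical value of 1.96 (one-sided 0.025 or two-sided 0.05) gives 87.1% (t) to 87.8% (z).
- *Two-sided 0.025:* a normal critical value of 2.241 gives 79.9% (t) to 81.2% (z).

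**HEI, full data.** Var = 121 × 0.20125 = 24.35; SE = 1.077; noncentrality 4.643. Power is 99.0-99.2% two-sided and 99.6% one-sided. The stated figure of more than 99% stands.

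**After 20% attrition.** The text does not say how the 20% is applied, so four readings were computed.

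| Reading | Centers × children per center | PA, two-sided 0.025 | PA, one-sided 0.025 | HEI, two-sided | HEI, one-sided |
|---|---|---|---|---|---|
| 20% of centers and 20% of remaining children | 67 × 6.4 | 64.0-65.9% | 74.3-75.5% | 94.2-95.0% | 96.9-97.3% |
| Centers only | 67 × 8 | 69.0-70.9% | 78.5-79.7% | 96.6-97.2% | 98.3-98.6% |
| About 20% of children in total, through both routes | 75 × 7.2 | 72.4-74.0% | 81.2-82.3% | 97.4-97.8% | 98.8-98.9% |
| Children only | 84 × 6.4 | 75.2-76.7% | 83.5-84.4% | 97.9-98.3% | 99.0-99.2% |
| *Stated* | | *81%* | *81%* | *98%* | *98%* |

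For the first row, PA: Var = 9 × 0.26469 = 2.382; SE = √(4 × 2.382/67) = 0.377; noncentrality 2.652. This reading leaves 67 × 6.4 = 429 of 672 children, a 36% loss.

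**Detectable PA difference, 80% power, two-sided 0.025 (normal).** Full data: 0.320 × (2.241 + 0.842) = 0.99 min/h. After loss at both levels: 0.377 × 3.083 = 1.16 min/h. With the t distribution these are 1.00 and 1.19.

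**Sensitivity to the clustering model, two-sided 0.025, full data.** Swapping the two ICCs gives 82.6% (t). Dropping the provider ICC gives 84.6-85.8%. Only a single ICC of 0.07 exceeds 88% (89.3-90.3%), and that discards the center ICC of 0.10 at the level of randomization.

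**The case against.** The strongest reply is that sidedness is not stated, so the inputs are not complete. H1a is directional, and a one-sided 2.5% test on the same inputs gives 87-88%, the stated figure. If in addition the 20% is total child loss spread over both routes, PA power is 81-82% and HEI power about 99%, so one consistent reading comes close to all four figures. This stands, and it is why the point is conditional. It does not settle the matter. A directional hypothesis is not a one-sided test, and the Analytical Plan is worded as a test of differences and reports 95% confidence intervals. Two one-sided 2.5% tests would also make the trial one-sided 5% overall, which is nowhere declared.

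A reader might infer that the alpha split was simply left out of the calculation. The documents do not show that. One-sided 0.025 and two-sided 0.05 share a critical value, A.8.3 says 0.025 was used, and a single ICC of 0.07 also comes near 88%. The cause cannot be recovered from the text.

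A reader might also take 64-66% as the power after attrition. It assumes that the two losses compound. A.8.3 and A.7.4 both name centers and children, but neither says that the losses multiply.

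Nor do the A.7.4 stopping zones for recruitment depend on these figures: they are percentages of a recruitment benchmark. Finally, A.8.3 describes this attrition as higher than expected, and the primary analysis is a mixed model on all available data. The 81% is itself a completers' figure, however, so the comparison here is like for like.

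**Conclusion.** The point holds, conditional on sidedness and on the attrition reading. Under two-sided 0.025, full-data PA power is 80-81%, about 7-8 points below the stated 88%. After 20% attrition it is 64-77% depending on the reading, and none reaches 81%. Under an undeclared one-sided 0.025, 88% stands. Loss at both levels then gives 74-76%, centers only falls 1-2 points short of 81%, and 81% is met only if the 20% is total child loss arising at least partly within retained centers.

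HEI is little affected. Full-data power is right. The 98% after attrition is too high if both levels lose 20% (94-95% two-sided, 97% one-sided), and is reached two-sided only when the loss is wholly or largely of children within centers.

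These results rest on the three-level formula, equal cluster sizes, and the ICCs and SDs as A.8.3 gives them. Full-data power near 80% is still conventional, so the error lies in the stated figures and not in the viability of the design.

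**What to change.** In A.8.3, state whether the 2.5% is one- or two-sided, and whether the 20% attrition means centers, children, both in succession, or total child loss.

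- **If two-sided:** restate PA power as about 80% at full data and 64-66% after loss at both levels (or the table's figure for the reading intended), and HEI as about 99% and 94-95%. Give the detectable PA difference at 80% power: about 1.0 min/h at full data and about 1.2 min/h after loss at both levels.
- **If one-sided:** declare it in A.8.1 and A.8.3. The 88% may then stand, but 81% must become 74-76%, or the attrition wording must change to the reading that supports it.

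Use the same figures wherever A.7.1 and A.7.4 weigh retention against power. The cost is a text amendment and a less favorable stated power. No added centers are required; for scale, 88% at two-sided 0.025 would take about 104.
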